#### Supervision visits

In order to ensure CYLs are supported to offer high-quality preschool programming to children, CYLs will receive monthly on-the-job supervision visits from their FO. Visits will last for the entire preschool session. The LIST members will in turn provide ongoing support and coaching to FOs by accompanying them on their preschool supervision visits once a month. The NCHD FOs use a supervision checklist tool during their visits to assess program quality and fidelity, and to provide constructive feedback to the CYL on her strengths and areas for improvement. Similarly, the LIST member uses a separate supervision checklist tool to observe and provide constructive feedback to the FO.

#### Refresher trainings for CYLs and FOs

Both CYLs and FOs will participate in 1-day professional development workshops or refresher trainings. For CYLs, these will be led by NCHD MTs, and for FOs these will be led by LIST members.
Core refresher trainings:
CYL refresher trainings: A set of core training topics including preschool routine, child progress forms, and preschool behavior management will be offered to CYLs to reinforce key ECCE skills. These are intended to be held quarterly.FO refresher trainings: A set of training topics including use of the supervisory checklist tool, child progress forms, and gender and youth-sensitive supervision are offered to FOs to ensure high-quality preschool supervision visits. These are intended to be held bi-annually.Needs-based training: Additional professional development workshops may be held to address observed needs of CYLs and FOs identified by NCHD and LIST members.

#### Annual CYL conference

An annual conference will be held for all CYLs in one of the four targeted districts. The conference will provide CYLs with a platform to meet their peers, share ideas, discuss career-related challenges and ideas, and brainstorm solutions. The purpose of the conference is threefold: (i) to promote female youth agency; (ii) to support female youth personal and professional development; and (iii) to showcase the CYLs’ work.

#### LEAPS response during emergencies and conflict

In the past, there have been cases of political unrest and major flooding in Pakistan, which has led schools to shut down for weeks [39]. Table 6 in Additional file 1 details the actions that LEAPS will undertake to support CYLs and LEAPS children in the event of emergency response.

### Study design

This transition-to-scale trial uses a stepped wedge cluster-randomized design with three steps to evaluate the impact of the LEAPS program on children’s school readiness and female youth development in 99 clusters. A cluster-randomized approach was selected as the point of intervention will be at the community level; therefore, this approach minimizes the potential for contamination between intervention and non-intervention recipients. A stepped wedge approach was selected as a pragmatic approach to support program implementation on a larger scale [40]. The LEAPS program will be introduced in clusters in a randomized sequence at three discrete timepoints over the course of the 31-month trial. At each of the three timepoints, 33 clusters will cross over from the control condition (i.e., NCHD services as usual) to the intervention condition (i.e., initiating the LEAPS program) (see Fig. 2). Once a cluster crosses over it will remain exposed (i.e., the program will remain in operation) for the duration of the trial. Each step will be 7 months in duration. In Sindh, the academic year runs from April to March, with longer holidays falling in May and June, and an extended enrolment period that runs from April to September. Our initial rollout is planned to align with this academic cycle. Prior to opening the LEAPS schools in each step, targeted clusters will undergo a transition period in which NCHD, with technical assistance from the LIST members, will initiate CYL recruitment and trainings, preschool space identification, and community sensitization activities. No concomitant care or interventions are prohibited during the trial due to the pragmatic design of the trial.

**Fig. 2 Fig2:**
[figure not shown]
Stepped wedge cluster-randomized trial timeline

### Cluster identification and randomization

A cluster is defined as the catchment area of an NCHD Feeder primary school. We restricted the study clusters to NCHD Feeder primary school catchment areas because the possibility to transition from ECCE to primary school was considered essential. The research team coordinated with the NCHD to compile a list of all villages across the four districts with NCHD Feeder schools (*n* = 119), excluding the villages from the LEAPS pilot trial. With the NCHD, the research team screened potential clusters against predefined exclusion criteria, including (i) lack of an eligible CYL candidate, (ii) safety and security concerns, (iii) lack of proper space for the preschool, or (iv) NCHD Feeder school had closed. Twenty clusters were excluded though this process. We applied stratified randomization to the 99 clusters using the 4 districts as strata with 3 blocks in each stratum. The 99 clusters were randomly assigned in blocks to one of the three steps (*n* = 33 clusters per step). The stratified randomization was completed using a computer-generated random allocation sequence in Excel. Block randomization was used to ensure that clusters were evenly dispersed by geography across each step, so that intervention rollout was feasible for implementation partners. The co-investigator and project Senior Statistician (CS) who conducted the randomization is not involved in any of the field activities. The final trial includes six clusters in Dadu, nine clusters in Sukkur, 28 clusters in Khairpur, and 56 clusters in Naushahro Feroze (Fig. 3).

**Fig. 3 Fig3:**
[figure not shown]
Map of Districts for the LEAPS Transition-to-Scale Trial in Rural Sindh. Note for Fig. 3: One cluster from district Khairpur was randomized with the district Naushahro Feroze clusters, as it was geographically closer and a multiple of 3 was needed in each group. This cluster fell under the responsibility of the Naushahro Feroze NCHD District Office

### Description of data collection activities & study sample

Data collection activities and the participant timeline are summarized in the SPIRIT figure (Table 1) [34]. The trial will include the following data collection activities:

**Table 1 Tab1:** SPIRIT figure depicting schedule of enrollment, interventions, and assessments. ^i^The population survey is a cross-sectional survey enrolling 11 children aged 4.5–5.5 years and their primary caregiver per cluster in each of the 99 clusters (total of 1089 child-caregiver dyads per round) conducted at four timepoints. ^ii^The school cohort is a closed cohort enrolling 10 LEAPS preschoolers and their primary caregiver per cluster (stratified by gender) in each of the 33 clusters receiving the intervention during Step 1 (total of 330 child-caregiver dyads). ^iii^An open cohort of youth participants will be enrolled in each of the steps (3 cohorts in total). Each cohort includes all Community Youth Leaders (CYLs) hired by NCHD, as well as two comparison youth participants per cluster (33 CYLs and 66 comparison youth per cohort; 99 CYLs and 198 comparison youth in total). *During the final 2 months of Steps 0, 1, and 2, the 33 clusters that are targeted for intervention rollout in the upcoming step will undergo a transition period to prepare for opening the LEAPS preschools, including recruiting and training CYLs, identifying the preschool space, and setting up the preschool classroom

	Study period				
Timepoints	Step 0	Step 1	Step 2	Step 3	Close out
	1–3 mo.*	4–10 mo.*	11–17 mo.*	18–24 mo.	25–31 mo.
**Cluster randomization**	X				
**Allocation**	X				
**Study phase**					
**33 clusters**	**Control***	**Intervention**	**Intervention**	**Intervention**	
**33 clusters**	**Control**	**Control***	**Intervention**	**Intervention**	
**33 clusters**	**Control**	**Control**	**Control***	**Intervention**	
**Assessments**					
**Child, population survey**^**i**^					
Demographics	X	X	X	X	
School readiness	X	X	X	X	
Executive functioning skills	X	X	X	X	
**Child, school cohort**^**ii**^					
Demographics		X		X	
School readiness		X		X	
Executive functioning skills		X		X	
**Youth cohorts**^**iii**^					
Demographics		X	X	X	
Personal and professional development		X	X	X	
Executive functioning skills		X	X	X	
Self-reported depressive symptoms		X	X	X	
**Mediators**					
Classroom structural and process quality			X	X	
**Other**					
Implementation/ cost/ system strengthening evaluations				X	

#### Population survey

A cross-sectional survey of child-caregiver dyads will be conducted at four timepoints: at baseline (Step 0; mos. 1–3) and again at the end of each consecutive step, with 7 months between data collection rounds. Eleven children aged 4.5–5.5 years and their caregivers will be enrolled in the population survey from each of the 99 clusters (1089 child-caregiver dyads total), regardless of the child’s enrollment in the LEAPS preschool program. The primary objective of the population survey will be to assess changes in the average school-readiness over time. With this trial design, rather than assessing program impact on specific individuals, we are aiming to assess the impact of LEAPS on local (cluster-level) school readiness, which is a function of both the proportion attending LEAPS and the impact on the treated. By including both LEAPS participants and children who are not participating in the LEAPS program, this design will allow us to separate treatment effects on the treated from average (intent-to-treat) effects at the population level. The sample will be drawn from village birth registries provided by NCHD, which will be verified (a) by cross-checking against birth registries from local community health workers; and (b) through household visits conducted by research team members. The sample will be re-drawn at each of the four data collection timepoints. Children may be enrolled for assessment at multiple timepoints. Assessors will use a random number generator to select 11 participants/cluster using the verified lists of eligible children prepared for each cluster. If a participant refuses, assessors will select the next participant in the random sequence.
Eligibility criteria: Child is age 4.5–5.5 years ± 2 weeks (i.e., 53.5–66.5 months at the time of the survey) and resides in the targeted villageExclusion criteria: Child or caregiver shows signs of severe clinical health condition or disability

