### Sample size and power calculation for stepped wedge cluster-randomized trial

A power calculation was conducted with respect to the changes in average child outcomes using representative population surveys, applying the methods as outlined by Hemming and Taljaard [70]. The primary study outcome is children’s school readiness as indexed by scores on the International Development and Early Learning Assessment (IDELA). An intraclass correlation coefficient (ICC) of 0.175 was calculated based on the results of the LEAPS efficacy trial [26] using total IDELA score at endline for the control group. With a fixed number of clusters (*n* = 99) and a step-size of three (*n* = 33 clusters randomized per step), we estimate that at least 8 children per cluster per round, or 792 children total per round, will need to be enrolled to detect a 0.3 SD effect size at 80% power. To achieve adequate power and take refusal rate into account, we will enroll 11 child-caregiver dyads per cluster for a total of 1089 child-caregiver dyads per round, which should detect a 0.3 SD effect size at 90% power with full recruitment. In other words, we estimated sufficient sample sizes to achieve at least 80% power with up to 30% refusal/under-recruitment rate in each round of the data collection under the intent-to-treat principle. This includes refusals from caregivers and children, or under-recruitment due to a decrease in children available at the point of data collection, particularly in smaller villages.

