### Analysis

#### Impact evaluation

The primary analysis will use the intent-to-treat principle. Baseline balance will be tested between randomized groups to see whether randomization was successful. The primary outcome, IDELA total score, will be computed for each individual using the parameter estimates from the Graded Response Model, as recommended by the tool developers. We will assess the effect of the LEAPS intervention using the analytical framework proposed by Hussey and Hughes [71] for analysis of stepped wedge cluster-randomized trials. Estimation of treatment effects will be obtained from a generalized linear mixed model (GLMM) to produce the mean difference in IDELA scores for LEAPS intervention versus control. The GLMM will include a fixed effect for stratified randomization group, a random effect for cluster, a fixed effect for time, and use an exchangeable correlation structure. In addition, the study will perform a set of sensitivity analyses to explore potential deviations from the basic SW-CRT model proposed by Hussy and Hughes [71]. The closed school cohort data will be to examine the changes in the average school readiness among children participating in the LEAPS preschool between baseline and endline. Longitudinal data collected for school cohort participants will be linked using participant IDs. The preschool classroom structural and process quality data and the child household characteristics will serve as predictors of interest in adjusted analyses. Youth cohort data will be analyzed to examine differences in outcomes over time among CYLs as compared to the youth comparison group. Longitudinal youth participant data will be linked using participant IDs. Analysis will account for CYLs’ length of program exposure and adjust for potential confounding variables, including age, education, marriage status, assets-based household socio-economic status, and household food insecurity. No interim analyses are planned.

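### The survey can assess the same child in two adjacent rounds, but the primary model has no child-level term; the SE is modestly misstated and some precision is lost.

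*Protocol article*

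**What the plan says.** In the Protocol article, Population survey, the survey is described as cross-sectional. It takes eleven children per cluster at four timepoints, "with 7 months between data collection rounds". The draw is fresh each time: "The sample will be re-drawn at each of the four data collection timepoints". A child sampled once is not barred from being sampled again: "Children may be enrolled for assessment at multiple timepoints". Eligibility is by age, "53.5–66.5 months at the time of the survey".

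The Impact evaluation section fixes the primary analysis: "We will assess the effect of the LEAPS intervention using the analytical framework proposed by Hussey and Hughes". Besides a fixed effect for the randomization stratum, the model has "a random effect for cluster, a fixed effect for time, and use an exchangeable correlation structure". No child-level term is listed. The same section says "Longitudinal data collected for school cohort participants will be linked using participant IDs" and makes a similar statement for the youth cohorts. It makes none for the population survey. It also promises sensitivity analyses around the basic stepped wedge model, without naming them.

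The sample size section uses an ICC of 0.175 and allows for "under-recruitment due to a decrease in children available at the point of data collection, particularly in smaller villages".

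**The concern.** The sampling rule makes the survey partly longitudinal, while the stated model treats it as purely cross-sectional. Under an exchangeable structure with a cluster effect only, any two scores in a cluster have correlation 0.175, whether they come from one child or two. Two scores of one child 7 months apart should be more alike than that. With a within-child residual correlation of 0.5 (assumed), the same-child correlation is 0.175 + 0.825 × 0.5 = 0.5875.

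Two things are at stake. The SE printed by the model is not the estimator's real SE. In addition, the before-and-after comparisons within repeat children, some of whom live in clusters that cross over between the two rounds, go unused.

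**Working it through.** **Inputs from the protocol.** 99 clusters, 33 per step, 4 rounds, 11 children per cluster per round (8 as the minimum), ICC 0.175, effect 0.3 SD, age window 53.5–66.5 months, spacing 7 months. **Assumed, because the article does not give them:** two-sided alpha 0.05, total SD 1, number of eligible children per cluster N, within-child residual correlation r, cluster autocorrelation. The stratum effect is left out of the calculation.

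**1. The plan's own power figures.** The Hussey–Hughes variance is I·s²(s² + T·t²) / [(I·U − W)s² + (U² + I·T·U − T·W − I·V)t²], where s² = 0.825/m and t² = 0.175. Here I = 99, T = 4, U = 33 × (3+2+1) = 198, W = 33² + 66² + 99² = 15,246 and V = 33 × (9+4+1) = 462. So I·U − W = 4,356, and the second bracket is 39,204 + 78,408 − 60,984 − 45,738 = 10,890.

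- m = 11: s² = 0.075. Variance = 99 × 0.075 × 0.775 / (326.7 + 1,905.75) = 5.754/2,232.45 = 0.002578, so SE = 0.0508. Then 0.3/0.0508 = 5.9 and power exceeds 99.9%.
- m = 8: s² = 0.1031. Variance = 8.199/2,354.96 = 0.003482, so SE = 0.0590 and power is 99.9%.

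The stated 90% and 80% are therefore not reproduced by this model with these inputs. That is a separate matter. It is relevant here only because it shows how much room there is for 0.3 SD.

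**2. How many repeats.** The share still eligible one round later is (66.5 − 53.5 − 7)/13 = 6/13 = 46%, if ages are spread evenly. Two rounds later is 14 months, which exceeds 13, so no child appears in three rounds. Expected repeats among 11 are 11 × (6/13) × (11/N):

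| Eligible per cluster N (assumed) | 11 | 15 | 20 | 30 | 60 |
|---|---|---|---|---|---|
| Expected repeats | 5.1 | 3.7 | 2.8 | 1.9 | 0.9 |

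**3. Effect on the SE, no cluster-by-period variation.** Let q children per cluster be shared between adjacent rounds. Each same-child pair adds 0.825·r to the covariance V. The cluster-only model absorbs the average of this. For q = 3, r = 0.5, 9 of the 946 pairs in a cluster are same-child pairs, so the fitted ICC becomes 0.175 + 9 × 0.4125/946 = 0.1789. With W the fitted exchangeable matrix:

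- model SE comes from (X′W⁻¹X)⁻¹;
- true SE comes from (X′W⁻¹X)⁻¹ X′W⁻¹VW⁻¹X (X′W⁻¹X)⁻¹;
- SE with child correlation modelled comes from (X′V⁻¹X)⁻¹.

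| q | r | Model SE | True SE | SE with child correlation | Model/true | True/child model | Type I error |
|---|---|---|---|---|---|---|---|
| 1 | 0.5 | 0.0507 | 0.0501 | 0.0487 | 1.013 | 1.03 | 4.7% |
| 2 | 0.5 | 0.0507 | 0.0494 | 0.0469 | 1.027 | 1.05 | 4.4% |
| 3 | 0.5 | 0.0507 | 0.0486 | 0.0453 | 1.042 | 1.07 | 4.1% |
| 5 | 0.7 | 0.0506 | 0.0456 | 0.0351 | 1.108 | 1.30 | 3.0% |

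The model SE is too large because the treatment contrast is largely within cluster over time, and positive correlation between rounds shrinks the variance of such contrasts.

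**4. With cluster-by-period variation.** Keeping q = 3 and r = 0.5 and letting the cluster effect decay between rounds:

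| Cluster autocorrelation (assumed) | 1 | 0.95 | 0.9 | 0.8 |
|---|---|---|---|---|
| Model SE / true SE | 1.04 | 0.99 | 0.94 | 0.87 |

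A small departure from 1 is enough to reverse the sign.

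**The case against.** **The error is small and conservative.** When the repeats are the only departure from the model, this stands. A reader might infer that ignoring repeated children inflates false positives. The calculation shows the opposite: type I error stays at or below 5%. At about 5.9 SEs for 0.3 SD, power is not in question either.

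**The interval is not necessarily too wide.** A reader might infer that the reported interval for the primary effect will be too wide. The documents do not support this as a net result. It holds with cluster autocorrelation 1, but at an assumed 0.9 the interval is too narrow despite three repeats per cluster. A child term alone would remove the conservative part and leave the other in place.

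**The gain is easy to overstate.** Comparing the child-model SE with the model's reported SE mixes misreporting with lost precision. For q = 3, r = 0.5 that comparison gives (0.0507/0.0453)² = 1.25. The real loss is measured from the true SE: (0.0486/0.0453)² = 1.15.

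**The size rests on absent figures.** Neither the number of eligible children per cluster nor the within-child correlation is given. The sample size section expects shortfalls in smaller villages but does not say how small or how many. The largest figures need short lists and high correlation together.

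**The aim is cluster-level, and the full protocol or SAP may add detail.** A re-drawn survey suits the stated population aim, and silence on survey ID linkage does not show that none exists. However, the article does list the terms of the primary model, and a child effect is not among them. Unspecified sensitivity analyses do not alter that primary model.

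**Conclusion.** The point holds as a modest misspecification of the primary model. The sampling rule permits same-child pairs in adjacent rounds, and the stated correlation structure has no place for them.

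Taken alone, for 1–3 repeats per cluster and r = 0.5, the model SE is about 1–4% too large and the true SE is about 3–8% above what a model with child correlation would give. With 5 repeats and r = 0.7 these become about 11% and 30%. Village list size and r are assumptions, and the figures assume cluster autocorrelation 1. Below that, the net error can go the other way.

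The repeats threaten neither the validity of the primary test nor power for 0.3 SD. The case for change is a correctly stated SE and cheap extra precision.

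**What to change.** - Keep one permanent child ID across the four survey rounds, matched on the village lists that are already verified each round.
- Add a random effect for child within cluster to the primary model, together with a cluster-by-period random effect or cluster-robust variance. Robust variance without the child term would correct the SE but not recover the precision.
- Adjust for the child's age at assessment. It is already collected as a covariate. A repeat child is about 7 months older at the second assessment, and the listed primary model has no age term.
- Report the number of repeat children in each round.

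The cost is ID matching on existing lists and a slightly more complex model. No additional children or visits are needed.

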#### School cohort

A closed cohort of 330 LEAPS children and their caregivers (10 children/cluster, stratified by gender) will be enrolled from the 33 clusters receiving the intervention in Step 1. The main purpose of the school cohort is to assess individual learning and growth trajectories among children participating in the program. Child-caregiver dyads will be enrolled and assessed during Step 1, after the intervention has been initiated in month 8 of the trial and followed up again at the end of Step 3 in month 24. Assessors will use a random number generator to randomly select five girls and five boys from the CYL’s enrolment register. If a participant refuses, the next participant in the random sequence will be invited. If fewer than five participants of one gender are registered in the LEAPS class, additional children of the other gender may be enrolled to meet the ten-student sample for that cluster.
Eligibility criteria: Child must be registered and regularly attending the LEAPS schoolExclusion criteria: Child or caregiver shows signs of severe clinical health condition or disability

#### Youth participants

A case:comparison design will be employed in order to examine program impacts on youth participants. In each step, we will enroll an open cohort comprising the 33 CYLs from the 33 clusters introducing the intervention in that step (one CYL/cluster), as well as 66 youth comparisons for a 1:2 CYL: youth comparison ratio (i.e., 3 youth cohorts (one/Step) enrolling 33 CYLs:66 youth comparisons; in total, 99 CYLs and 198 youth comparisons enrolled). In each step, the CYLs will be enrolled in the evaluation and assessed as they are hired by NCHD, during the month before and first month of the step (i.e., in mos. 3–4 for Step 1, in mos. 10–11 for Step 2, and in mos. 17–18 for Step 3). The youth comparisons will be enrolled and assessed beginning the month before through the first 2 months of the step (i.e., in mos. 3–5 for Step 1, in mos. 10–12 for Step 2, and in mos. 17–19 for Step 3). Youth cohort participants will be followed up every 7 months. Given the context, some dropouts are expected, particularly among comparison youth. The sampling ratio of 2 comparison per 1 CYL is intended to compensate for these dropout levels. If a CYL drops out of the LEAPS program after having initiated her in-classroom teaching experience, she will be invited to remain in the evaluation as part of the CYL cohort. If a CYL drops out of the LEAPS program prior to completing her basic training (i.e., prior to having any in-classroom experience), she will be invited to remain in the evaluation as part of the comparison youth cohort. Similarly, if NCHD hires a comparison youth as a CYL, she will be invited to continue in the study as a CYL, and a new comparison youth will be identified and enrolled.

Youth comparisons will be identified using a screening tool during CYL recruitment activities and through door-to-door household visits. The screening tool for youth comparisons includes a series of questions and short case study exercises to ensure that the participant (i) meets the same gender, age, and education requirements as the CYL, (ii) has support from her family to pursue employment outside of the workplace (as is the case with CYLs), and (iii) demonstrates confidence, and advocacy and problem-solving skills. The tool takes approximately 15 min to implement. These screening criteria represent the qualities that the research team considers most central to the CYL role. Given that CYLs may be positive deviants in their community and have demonstrated high-selection workshop performance relative to their peers, the purpose of the screening tool is to ensure to the best of our ability that youth participants are a fair comparison for CYLs in terms of family environment and skillsets baseline.
Eligibility criteria:
◦ CYLs must be hired by NCHD.◦ Youth comparisons must be female, aged 18–24 years ± 2 weeks, have a minimum tenth grade education, have support from family members to pursue employment, meet capacity-checks for confidence, advocacy, and problem-solving skills, and have no in-classroom teaching experience with LEAPS.Exclusion criteria: Youth participant shows signs of severe clinical health condition or disability

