#### CYL recruitment

Following the TOT, district managers and FOs will initiate the CYL recruitment process in their catchment areas. NCHD will engage Feeder school teachers, community health workers, village leaders, and other community members to inquire about potential female youth candidates meeting the CYL recruitment criteria (i.e., aged 18 to 24 years old, have completed Grade 10 schooling, have their family’s support to participate). Candidates will be invited to attend a local CYL recruitment workshop. Recruitment workshops will be led by district managers and FOs, with support from LIST members, and comprise a range of activities designed to assess candidates’ literacy, numeracy, general knowledge, attitudes toward working with young children, problem solving, creativity, communication, and leadership potential. Youth participants’ performance on workshop activities will be scored using a standardized rubric. Participants who meet the CYL recruitment criteria and have the highest scores will be selected as the CYL.

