#### Data collection procedures for youth participant assessments

CYLs will be issued an invitation to the study during the recruitment and training process. Assessors will issue invitations to comparison youth after completing the screening tool. The youth participant will either be enrolled and assessed on site or at a follow-up appointment, as is practical for the participant. The assessment will be conducted either at a recruitment workshop, training session, or during a home visit with the youth participant. All consecutive follow-up assessments will be conducted at the participant’s household, at the LEAPS school, or at an alternative community space identified for assessments. Location of assessments will be selected based on convenience for the youth participant and the availability of private space. All questionnaires will be collected using tablets. Executive functioning assessments will be conducted manually and later entered in tablets. Youth participants will receive a thank you gift (e.g., a LEAPS mug) and refreshments for participation.

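### The protocol does not ensure that a CYL's enrolment assessment comes before her training and first weeks of teaching, so the youth baseline may already contain part of the programme effect

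*Protocol article*

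**What the plan says.** All references are to the protocol article.

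- **Preparation period.** The note to Table 1 gives the 33 clusters due to open a transition period in the last two months of the preceding step, "including recruiting and training CYLs, identifying the preschool space, and setting up the preschool classroom".
- **CYL enrolment window.** Under Youth participants, CYLs are enrolled and "assessed as they are hired by NCHD, during the month before and first month of the step": months 3–4, 10–11 and 17–18 for the three steps.
- **Comparison window.** Comparison youth are "enrolled and assessed beginning the month before through the first 2 months of the step", one month longer.
- **Invitation and venue.** Under Data collection procedures for youth participant assessments: "CYLs will be issued an invitation to the study during the recruitment and training process". On the place: "The assessment will be conducted either at a recruitment workshop, training session, or during a home visit with the youth participant".
- **Selection.** Under CYL recruitment: "Participants who meet the CYL recruitment criteria and have the highest scores will be selected as the CYL". The Youth participants section concedes that CYLs may stand out from their peers, and adds a screening tool meant to give a "fair comparison for CYLs in terms of family environment and skillsets baseline".
- **Analysis.** Under Impact evaluation, linked longitudinal data are used to compare outcomes over time between CYLs and comparison youth. The analysis accounts for CYLs' length of exposure and adjusts for confounders, "including age, education, marriage status, assets-based household socio-economic status, and household food insecurity".

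**The concern.** A contrast of outcomes over time needs a first measurement that the programme has not yet touched. The 12-day training is part of the vocational intervention, and hire brings a salary and a new role. Several youth outcomes (self-esteem, self-efficacy, professional growth, aspirations, depressive symptoms) could plausibly respond to being hired and trained, before any teaching. If they do, that part of the effect sits in the CYLs' enrolment score and is subtracted when change is computed. Comparison youth have no such exposure, so the loss falls on one side only.

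This contrast is the quantitative evidence for Objective 2, the effect on female youth development. A later analysis plan can limit the damage, but it cannot recover a pre-training score that was never taken.

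**Working it through.** **Timing.** Table 1 gives Step 0 as months 1–3, Step 1 as 4–10, Step 2 as 11–17 and Step 3 as 18–24. The last two months of each preceding step follow by counting.

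| Cohort | Recruitment and training | CYL enrolment window | Overlap with preparation | First month of the step |
|---|---|---|---|---|
| Step 1 | months 2–3 | months 3–4 | month 3 | month 4 |
| Step 2 | months 9–10 | months 10–11 | month 10 | month 11 |
| Step 3 | months 16–17 | months 17–18 | month 17 | month 18 |

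Two things follow.

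1. The window covers the second preparation month and the first month of the step. The first preparation month (2, 9, 16) lies outside it. A recruitment workshop held then could not host an enrolment assessment within the stated window.
2. Table 1 marks no youth assessment under Step 0 and first marks one under Step 1, whereas the Youth participants section starts in month 3. Read literally, the table places every Step 1 enrolment assessment after the preparation period. The two places should be reconciled.

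**Direction and size.** The documents give no figure for this point, so there is none to reproduce. The following is illustration only. Let

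- E = true programme effect at follow-up (assumed 0.30 SD);
- c = average share of E already present in CYLs' enrolment scores (assumed). It is the product of the share of CYLs assessed late and the share of the effect those CYLs have gained; for example 0.5 × 0.2 = 0.10;
- g = gap between CYLs and comparison youth due to selection alone, taken as constant over time (assumed).

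Expected gap at enrolment = g + cE. Expected gap at follow-up = g + E. The difference over time is (g + E) − (g + cE) = E(1 − c), whatever g is.

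| c | E(1 − c), SD |
|---|---|
| 0 | 0.30 |
| 0.10 | 0.27 |
| 0.25 | 0.225 |
| 0.50 | 0.15 |

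For scale, the standard error of a simple 99 versus 198 difference is √(1/99 + 1/198) = 0.123 SD, ignoring dropout and repeated measures. The shortfall runs from 0.03 SD (c = 0.10) to 0.15 SD (c = 0.50), that is from about a quarter of a standard error to somewhat more than one.

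**Use of the enrolment score.** With a clean enrolment score (c = 0):

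- ignoring it gives g + E: 0.30 + 0.2 = 0.50 SD for g = 0.2, and 0.30 + 0.5 = 0.80 SD for g = 0.5;
- using it as a covariate with an assumed slope of 0.6 gives g + E − 0.6g: 0.50 − 0.12 = 0.38 SD and 0.80 − 0.30 = 0.50 SD.

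So the score removes part of the selection gap, not all. Using it as the first repeated measure removes the gap fully only under the assumption above that g does not change over time.

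**The case against.** The strongest reply on timing is that assessment is tied to hire. The part of the window inside the step may exist only for late hires, the recruitment workshop is an allowed venue, and the protocol provides for a CYL who leaves before finishing basic training to stay in the evaluation as a comparison youth. Some CYLs are therefore expected to be enrolled before training ends. This stands: contamination is possible for some CYLs, not shown for all. It does not supply the missing rule, because hire may come shortly before training, during it or after it, and a training session is named as a venue.

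Three stronger readings are tempting and not supported.

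- **That the youth model leaves out the enrolment score.** The article fixes no youth model. It describes a comparison of linked outcomes over time, which may use the enrolment score as the first repeated measure, and its list of confounders is open-ended. The specification may stand in a document not shown.
- **That dilution from a late baseline and inflation from selection add up in one result.** Dilution needs an analysis that uses the enrolment score; the full selection gap appears only in one that ignores it.
- **That CYLs are selected on the trial outcomes with nothing done about it.** They are selected on a workshop rubric. Comparison youth are screened for the same gender, age and education requirements, family support, confidence, advocacy and problem-solving. The screen is a short capacity check rather than the rubric, so it handles selection only in part.

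The longer comparison window is not a source of contamination either, since those youth are not exposed.

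**Conclusion.** The timing point holds. As written, the protocol lets a CYL's enrolment score be taken after hire, during training or in the first month of the step, and no rule prevents it. A difference over time would then be understated, provided that hire and training move scores in the same direction as the full programme. The size cannot be derived from the documents: the 0.03 to 0.15 SD shortfall rests on an assumed effect of 0.30 SD and an assumed 10% to 50% of it already gained on average.

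The consequence is limited to secondary, openly non-randomized youth outcomes; the primary IDELA analysis is not affected. The reliance on the enrolment score is greatest in the Step 3 cohort. It enrols in months 17–19, is followed at 7-month intervals, and has no youth assessment marked in Table 1 after month 24, so it has at most about one follow-up. This is a worthwhile, low-cost improvement, not a flaw that undermines the trial.

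**What to change.** 1. **Timing rule.** State that each CYL's enrolment assessment is completed before day 1 of the 12-day training. The recruitment workshop is already a permitted venue, but the CYL window must then open early enough to cover workshops held in the first preparation month. Bring Table 1 into line with the text.
2. **Data already collected.** Use each CYL's assessment date relative to the start of training to define when exposure begins, which the exposure-length adjustment needs in any case. Repeat the youth analysis excluding CYLs assessed after training began.
3. **Model wording.** State that the pre-training enrolment score of each outcome enters the youth model, as first repeated measure or as covariate, and acknowledge that this will not fully remove selection bias. A score taken after training began should not be treated as a clean baseline.

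**Cost.** An existing assessment is moved, and a few candidates who are not finally hired may be assessed. The sensitivity analysis loses precision: if half of the CYLs were excluded (an assumption), the standard error would rise from 0.123 to √(1/49.5 + 1/198) = 0.159 SD. CYLs assessed late may also differ from the others, for instance as late hires, so that analysis is a check and not a replacement.
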